### Outcomes

2.8

-The primary outcome will be the change of lesions 2 months after randomization.

Change of lesions will be defined as regression or progression of the size of the lesion seen on VIA. Regression can be partial or complete when there is a total disappearance of the lesion also called remission. On cytology, regression will be defined as improvement from high-grade to low-grade CIN and remission will be defined as improvement from any grade of CIN to no CIN.

-The secondary outcomes will be:The secondary outcomes will be•Clearance of HPV at 2 months post-randomization,•Correlation between change of lesions change in HPV DNA at 2 months post-randomization,•Change in HPV viral particle load 6 months post-randomization.-The tertiary outcome will be the number of patients with adverse effect.

An adverse effect (AE) will be defined as any unfavourable and unintended sign, symptom, or disease temporally associated with the use of the product administered. A causality assessment of the AEs will be done in accordance with the guidelines of the WHO–Uppsala Monitoring Centre.

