### Sample size

2.9

Assuming a lesion regression rate of 50% in the non-interventional group and 70% in the antiviral drug group at 2 months post-treatment, a minimum sample size of 163 patients is needed to show with 95% power a difference between both groups. To allow for up to 10% drop-outs or unevaluable patients, we will recruit at least 190 patients in each arm. We expect 20% of the women to be HPV positive, of whom 10% with and 10% without lesions, indicating that over 1900 women will have to be enrolled to obtain the required sample size.

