### Statistical analyses

2.10

Data will be double-entered and cleaned in EpiInfo (version 6.04 b, Centers for Diseases Control and Prevention). Proportions will be compared using the x^2^ or Fisher's exact tests (when required). Student's *t*-test will be used for continuous variables. A Mc Nemar or paired *t*test will be used for within-patient comparisons where approriate. Non-normally distributed variables will be transformed, or nonparametric tests (Wilcoxon or Kruskal-Wallis) will be used. Stepwise multivariate analyses will be performed, and all possible interactions up to order 2 will be tested. All reported *P* values will be 2-sided. For all statistical analyses a *P* value of ≤0.05 will be considered as statistically significant.

All analyses will be performed using the STATA statistical analysis software packages (Version 12; Stata Corp, Lakeway, College Station, Texas, USA).

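### Stepwise selection and testing of every two-way interaction at an unadjusted 0.05 make P values and intervals for the selected covariates and interactions too optimistic

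*Protocol article*

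**What the plan says.** Section 2.10 (Statistical analyses) of the Protocol article first covers simple comparisons: "Proportions will be compared using the x^2^ or Fisher's exact tests (when required"), with t-tests, paired tests and nonparametric alternatives for other data. It then adds: "Stepwise multivariate analyses will be performed, and all possible interactions up to order 2 will be tested". On significance it says that all reported P "values will be 2-sided" and, for every analysis, that a P "value of ≤0.05 will be considered as statistically significant".

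Section 2.8 defines the endpoint: "The primary outcome will be the change of lesions 2 months after randomization". Section 2.9 sizes the trial on two proportions: "Assuming a lesion regression rate of 50% in the non-interventional group and 70% in the antiviral drug group" at 2 months.

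The article does not say which outcome or population the stepwise models serve, how many covariates are candidates, or whether treatment is forced into the model.

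**The concern.** The multivariable step lets the data choose which covariates and products stay in the model, then judges those terms at 0.05 as if the model had been fixed in advance. A term kept because its P value was small will have an estimate that is on average too far from zero and an interval that ignores the selection. Testing every pair also multiplies the chances of a false positive.

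What is at stake is the adjusted model and any subgroup claim drawn from it. Such a claim is foreseeable. The Discussion says that ideally only HPV-positive women would be randomized, but that VIA has to be used because HPV results take months. Whether AV2 works differently by HPV status or cytology grade is therefore a natural question once the results arrive. The abstract's conclusion expects the findings to guide screening and treatment algorithms, so a spurious subgroup result could carry weight.

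**Working it through.** **The plan's own figure.** Inputs from Section 2.9: 50% and 70% regression, 95% power; from Section 2.10: two-sided 0.05.

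- Without continuity correction, n = [1.960·√(2·0.6·0.4) + 1.645·√(0.25 + 0.21)]² / 0.20² = (1.358 + 1.116)² / 0.04 ≈ 153 per arm.
- With continuity correction, n′ = (n/4)·[1 + √(1 + 4/(n·0.20))]² ≈ 163 per arm, which matches the stated 163.
- Allowing for 10% loss, 163/0.9 = 181.1, so 182; the planned 190 per arm covers it.

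The trial is thus sized for an unadjusted comparison of two proportions, and the model search does not enter that calculation.

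**Error rate of the interaction search.** The article states no such rate. Let p be the number of candidate covariates besides treatment. This is an assumption, so a range is shown.

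- All two-way pairs among treatment and p covariates: k = p(p + 1)/2.
- Treatment-by-covariate pairs only: k = p.
- Chance of at least one false positive among k independent tests: 1 − 0.95^k.

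| p | All pairs k | Any false interaction | False treatment interaction |
|---|---|---|---|
| 3 | 6 | 26% | 14% |
| 4 | 10 | 40% | 19% |
| 5 | 15 | 54% | 23% |
| 6 | 21 | 66% | 26% |
| 8 | 36 | 84% | 34% |
| 10 | 55 | 94% | 40% |

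Any false interaction passes 50% from p = 5. A false treatment interaction passes 50% only at p = 14 (49% at 13, 51% at 14). One prespecified interaction test carries 5%.

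A count of six is plausible from the article itself: age, cytology category, HPV detection, HPV 16/18 typing, viral load and VIA lesion size. The article does not list these as candidates.

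**Check by simulation.** Forward stepwise logistic regression with 326 women (2 × 163), independent normal covariates with no effect, treatment forced in, entry at 0.05, 1,500 null trials per setting:

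| p | Any false interaction kept | False treatment interaction kept | False main-effect covariate kept | Treatment main effect significant |
|---|---|---|---|---|
| 3 | 26% | 15% | 13% | 5.4% |
| 5 | 54% | 22% | 22% | 6.5% |
| 8 | 85% | 36% | 32% | 5.7% |
| 10 | 94% | 45% | 44% | 4.7% |

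The simulation agrees closely with the formula for any interaction and gives slightly more false treatment interactions at p = 8 and 10. Nominal 95% intervals for the selected null terms contained the true value of zero only about 3–5% of the time. That is nearly automatic, since a null term is kept because its test rejects zero, but it shows why such intervals cannot be read at face value. The treatment main effect, when forced in, stayed close to 5%.

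**The case against.** Four points can be made for the plan.

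1. *The main comparison is protected.* Section 2.10 names chi-square or Fisher tests for proportions, and the sample size fits such a test. This stands. A reader might infer that the efficacy conclusion itself rests on a data-driven model, or that stepwise selection could drop treatment. The article says neither, and the randomized contrast does not visibly depend on the search.

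2. *The covariate count is unknown.* This also stands. A reader might infer that most trials run this way would report a spurious treatment interaction. The figures do not support that: with 3 to 10 covariates the chance is about 14–40% by formula. The larger percentages count all pairs, most of which do not involve treatment (15 of 21 with six covariates).

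3. *The sentence may concern something else.* It names no outcome or population, and the study will also report HPV prevalence in more than 1900 screened women, so it could cover risk-factor modelling. That is possible. The false-positive rate per test does not depend on sample size, however: five null covariates without treatment still give 10 pairs and 1 − 0.95^10 = 40%. The wording does not exclude models of the treatment effect.

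4. *Details belong in an analysis plan.* Candidate lists and entry criteria may well be in a document not shown, and their absence is not criticized. But stepwise selection, the testing of all possible pairs and the common 0.05 threshold are positive statements in the article, so the point does not rest on an omission.

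**Conclusion.** The point holds for the terms that the search selects. As written, Section 2.10 treats selected covariates and interactions as significant at an unadjusted two-sided 0.05, and their P values and intervals are too optimistic.

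The size depends on the assumed number of covariates. With 3 to 10 independent null covariates plus treatment, at least one false interaction of some kind arises in about 26–94% of trials, and at least one false treatment interaction in about 14–40%. Correlated covariates, as the HPV variables would be, would change these rates. Repeating the search for further outcomes would add more chances of a false result.

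The consequence is limited to adjusted-model and subgroup claims. The unadjusted comparison of regression rates, which appears to be the main analysis, keeps its error rate. The change should be made, but the point does not undermine the trial's main test.

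**What to change.** Drop stepwise selection for any model that estimates the treatment effect. In its place:

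- Prespecify one model with treatment forced in and a short fixed list of variables from data or specimens collected before randomization, for example age, baseline cytology category and baseline HPV status.
- Prespecify one or very few treatment interactions, for example treatment by baseline HPV status.
- Report every other interaction as exploratory, with estimates and intervals and no significance claim.

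The listed variables and interaction are examples; another short set, fixed before unblinding, would serve as well. If the stepwise sentence was meant only for risk-factor modelling in the screened women, say so and label that work exploratory.

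The cost is wording in the protocol or analysis plan. It needs no extra data, visits or patients, and the sample size is unchanged.

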### Ethical issues

2.11

The KINVAV study has been approved by the Institutional Ethical Committees /Institutional Review Board (IEC/IRB) of both the University of Kinshasa School of Public Health (Kinshasa, DRC) and the Antwerp University Hospital (Antwerp, Belgium), and registered in ClinicalTrials.gov (NCT02346227). It will be conducted in full agreement with the principles of the “Declaration of Helsinki” and subsequent relevant amendments. All participants will provide written informed consent before entering the trial.

## Discussion

3

In this trial, we will randomize women based on VIA which is known to be a subjective test. But according to the WHO studies, VIA does show better performance that allow its use as a cervical cancer screening test, especially in the frame of « see and treat approach » (SAT) [16], [17], [18].

For our study, the ideal process should be to start with HPV testing and secondarily randomize only HPV positive women. Unfortunately, real time HPV test such as Care HPV^®^ test (Qiagen) is not available yet in DRC. Plus, we need to prioritize the SAT approach which minimizes lost to follow-ups and all the difficulties encountered when women have to be recalled for results. For instance, in Africa, mothers are the pivot in the life of the family, they go to the crops, they travel for small businesses and all these situations possibly tend to affect follow-up rates.

Moreover, in our institution we are not able to perform HPV testing needed in this study yet. The samples will be shipped to South Africa for both LBC and HPV testing and it will take some months to get the results back. So, we cannot rely on HPV testing for randomization. We will thus randomize based on VIA test whose results are immediate. According to the natural history of cervical cancer, it takes 7–20 years for cervical HPV infection or dysplasia to lead to cervical cancer and a high proportion of HPV infection and mild dysplasia may regress spontaneously. During the two-months follow-up period we will detect all women with cervical dysplasia, even in the placebo arm, and treat them accordingly by cryotherapy which is a standardized treatment method used for the treatment of precancerous lesions. For those reasons, placebo can be safely used.

This study will be the first large-scaled study in Kinshasa to report on HPV prevalence and genotyping in DRC. One limitation for this study is the fact that instead of cytology or hpv testing results, randomization will be based on VIA which is a subjective test.

Finally, when we will get all the results concerning LBC and HPV testing, we will recall women to inform them of their results and treat those in need with standard treatment until we clear all precancerous lesions.

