**Methods:**

Women will undergo cytology sampling, HPV testing and Visual inspection of the cervix after application of 5% acetic acid (VIA). VIA-positive women will be randomized to one of two groups to receive treatment by either AV2^®^or placebo. They will undergo control examinations after two months and after six months. In case of persistent lesions on VIA, treatment by cryotherapy will be done. The primary outcomes will be the change of lesions, the clearance of HPV DNA, and the correlation of the two 2 months after treatment with AV2^®^.

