### Procedures and follow-up (Fig. 1)

2.3

Prior to the start of the study, a basic training of the doctors and nurses involved will be organized. This training will encompass Good Clinical Practice (GCP), collection of liquid-based cytology sample with cytobrushes, and VIA and cryotherapy procedures.

Women aged 25 and over will be invited to participate in a community cervical cancer screening programme. After giving their informed consent, eligible women will be examined by a trained doctor. The procedure will be performed while the woman lies in the lithotomy position on the examination table. After the cervix is exposed by a speculum inserted in the vagina, the doctor will collect a LBC specimen using the Thinprep PreservCyt solution^®^ (Hologic, Marlborough,USA), immediately after LBC sampling, VIA will be performed. Its results will be reported according to the WHO criteria and will serve for randomization. The results for LBC and HPV testing will not be available at this moment.

VIA-negative women will not be randomized and will receive no treatment. VIA-positive women will be randomized to one of two groups to receive either AV2^®^ or placebo. All randomized women will be followed-up and recalled after two months for repeat LBC and VIA. Women remaining positive on VIA at this stage will be treated by cryotherapy.

At six months' follow-up, women will be assessed in the same manner regarding VIA and LBC. The study will end at this stage. At each stage, the examinators will be blind to the previous results concerning the patient. At the end of the study, All women who will test positive for cervical lesions or HPV will be properly treated according to standard protocols and resources.

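### The placebo rationale says all dysplasia is found and treated within two months, but two-month cryotherapy depends on VIA alone and cytology results arrive later

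*Protocol article*

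**What the plan says.** The Discussion gives two reasons why a placebo arm is acceptable. The first is natural history: 7–20 years to cancer, with frequent spontaneous regression of HPV infection and mild dysplasia. The second is "During the two-months follow-up period we will detect all women with cervical dysplasia, even in the placebo arm, and treat them accordingly by cryotherapy". It then concludes: "For those reasons, placebo can be safely used".

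The treatment rules are these:

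- **Two months.** LBC and VIA are both repeated. The abstract (Methods) says "In case of persistent lesions on VIA, treatment by cryotherapy will be done", and section 2.3 says "Women remaining positive on VIA at this stage will be treated by cryotherapy". No cytology criterion is attached to treatment at this visit.
- **Six months.** VIA and LBC are repeated, and then "The study will end at this stage".
- **After that.** Section 2.3 says "At the end of the study, All women who will test positive for cervical lesions or HPV will be properly treated". The Discussion says that "when we will get all the results concerning LBC and HPV testing, we will recall women to inform them of their results" and that women in need will then be treated.

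On laboratory time, the Discussion says of the samples sent to South Africa that "it will take some months to get the results back". On the accuracy of VIA, section 1 cites a meta-analysis of asymptomatic screened women: sensitivity 80% (79%–82%) and specificity 92% (91%–92%) at the CIN2 threshold, with better performance in more severe disease.

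**The concern.** The second reason claims a safety property: no woman with dysplasia, on placebo or active drug, leaves the two-month period undetected and untreated. The rules treat only the women whom VIA picks up at that visit. Consider a woman who is VIA-negative at two months but whose LBC from the same visit shows a high-grade lesion. She is not treated at that visit, and the text names no treatment point for her cytology before the end of the study or the arrival of all results.

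Two things are at stake. A reader weighing the placebo arm is given an assurance that the design does not provide. And a high-grade result could be in hand for some weeks with no stated rule to act on it. The trial is listed as recruiting, so both can still be put right.

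**Working it through.** The plan gives no figure for this claim, so there is none to reproduce. The check compares the claim with the rules and then bounds the delay.

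**1. Can the two-month visit find all dysplasia?**

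- Trigger for treatment: VIA positive (abstract; section 2.3).
- Share missed by one VIA reading = 1 − sensitivity. With section 1's figures: 1 − 0.80 = 0.20, with range 1 − 0.82 = 0.18 to 1 − 0.79 = 0.21.
- This carries screening sensitivity over to a repeat reading in women who were VIA-positive at entry, which the documents do not establish. The conclusion needs only a sensitivity below 100%.

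**2. Can LBC fill the gap at that visit?** No. The sample is taken there, but the result takes some months. Cytology can add cases only after the two-month period has ended.

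**3. When is that cytology acted on?** There are two stated points: study end (section 2.3) and when all results are in (Discussion). Even if the second is read as action on each result as it arrives, action comes after two months. No reading makes the two-month claim true.

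**4. How much delay could a rule remove?** Assumptions: both phrases are read for the individual woman, and laboratory time L is 2 to 4 months (the documents give no number).

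- Two-month visit: week 8.7. Six-month visit: week 26.1. Gap: 26.1 − 8.7 = 17.4 weeks.
- Her two-month report is available at week 8.7 + L.
- *Results acted on as they arrive:* delay after the report = 0.
- *Treated at her six-month visit:* delay = 17.4 − L.

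| L | L in weeks | Delay after report |
|---|---|---|
| 2 months | 8.7 | 8.7 weeks |
| 3 months | 13.0 | 4.3 weeks |
| 4 months | 17.4 | 0 weeks |

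- *Recall waits for her own six-month LBC:* delay = (26.1 + L) − (8.7 + L) = 17.4 weeks, whatever L is.

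The range is 0 to about 17 weeks. It would be longer only if study end or all results were meant study-wide.

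**The case against.** The strongest reply is that this is one over-broad phrase in a passage that discloses its own limits. The Discussion calls VIA subjective, says that laboratory results are slow, and promises a recall with treatment until precancerous lesions are cleared. Natural history supports placebo without the disputed sentence. The six-month VIA is a real second look, and VIA is said to be more sensitive in more severe disease. All of this stands and is why the point is minor. It does not make the two-month statement true.

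A second reply is that result handling is operational detail which an article leaves to the full protocol. That is fair as to who receives a report and how recall works. But the article does state when positive women are treated, and those stated times conflict with the stated assurance.

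Four stronger readings are tempting, and the documents do not support them:

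- *Results are withheld until study end.* Nothing says so. The text only names no earlier trigger.
- *A known number of placebo women would be missed.* This needs a VIA-positive rate among screened women, which is not given; the 10% in section 2.9 concerns HPV-positive women with lesions. Solving 0.80p + 0.08(1 − p) = v for CIN2+ prevalence p, and taking 190 × 0.80p / v, gives 0 CIN2+ women in a 190-woman arm at v = 8%, about 42 at 10% and about 70 at 12%. Persistence at two months, repeat-VIA sensitivity and cytology yield are also unknown. The 50% in section 2.9 is lesion regression, which under section 2.8 may be partial.
- *The ethics committees were misinformed.* Section 2.11 records two approvals, not the text that was reviewed.
- *Placebo is unsafe.* Slow progression and the later safeguards argue against that.

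**Conclusion.** The point holds as a minor correction to the safety rationale, with a small safety rule attached. The contradiction comes from the text alone: VIA is the only two-month trigger, VIA is imperfect, and cytology is late. It rests on no estimate of case numbers, and none is offered.

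The size is the avoidable delay after a high-grade two-month report: nothing on the most favourable reading, and about 17 weeks if recall waits for the woman's own six-month LBC. That range assumes a turnaround of 2 to 4 months and a per-woman reading of both treatment points. Against a stated progression time of 7–20 years this is modest, and it gives no reason to abandon placebo.

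**What to change.** 1. Replace the disputed sentence in the Discussion with: *Women still VIA-positive at two months receive cryotherapy; VIA-negative women whose two-month LBC is HSIL or worse are recalled and treated when that result is reported.* Leave the natural-history argument as it is.
2. Add to section 2.3 that a two-month LBC of HSIL or worse, in a woman who has not had cryotherapy, is acted on at receipt by an existing clinician who is not her outcome examiner, and not held for study end or the full set of results. Treatment arm and outcome examiners stay blinded.

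The cost is a short amendment with ethics notification and one result-handling step. No new test is needed, because the LBC is already collected. The two-month primary outcome is unaffected, since it is recorded before any such recall. The downside is a few extra recalls, and a few more women treated before the six-month viral load is measured. That outcome already includes women given cryotherapy at two months, so the added treatment should be recorded in the same way.

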## Trial status

Recruiting
